### Screening

Individuals with type 1 diabetes are monitored at their own clinic and receive verbal or written information about the study during a visit at the hospital, or written information via mail and verbal information via telephone. If individuals are interested in participating, verbal and written informed consent will be obtained from each individual by an investigator (physician) at the study site. During the screening visit, inclusion and exclusion criteria will be examined. Major inclusion criteria are diagnosis of type 1 diabetes and first injection of insulin within 100 days prior to screening, age 18–45 years old, presence of at least one of the autoantibodies (insulin/IAA, GAD-65, ZnT8 or IA-2) at clinical practice or at screening and have a remaining stimulated peak C-peptide >0.20 nmol/L during a mixed meal tolerance test (MMTT). For all inclusion and exclusion criteria, see table 1.

**Table 1 T1:** Inclusion and exclusion criteria

Inclusion criteria	Exclusion criteria

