### Study visits

The visit schedule will be as follows: randomisation, week 2, 4, 13, 26, 39 and 52. MMTT will be performed at randomisation, week 4, 26 and 52. At all visits, physical examinations will be performed and HbA1c collected. Blood pressure and weight will be taken at all visits except week 2. A detailed description of the trial procedures is provided in table 2. Additionally, participants will complete a series of questionnaires evaluating intervention treatment satisfaction, well-being, hypoglycaemia confidence, diabetes-related distress and physical activity at the study site:

Diabetes Treatment Satisfaction Questionnaire (DTSQ) is an 8-item scale measuring aspects of satisfaction scored on a 7-point Likert scale, including domains of current treatment satisfaction, convenience of treatment, understanding of diabetes, recommendation of treatment and continuation of treatment. Two versions will be used: the DTSQs and DTSQc. DTSQs is used to record current treatment satisfaction throughout the trial and the DTSQc is used to retrospectively compare the treatment arms at week 52.^16^

**Table 2 T2:** Trial procedures

	Patient info (two visits)	Screening visit (fasting*)	Baseline randomisation (fasting)	Week 2 Follow-up±1 week	Week 4 Follow-up±10 days (fasting)	Week 13 Follow-up±2 weeks	Week 26 Follow-up±2 weeks (fasting)	Week 39 Follow-up±2 weeks	Week 52 Follow-up±2 weeks (fasting)		Weeks 104 and 208 Extension phase (±3 months) (fasting)	
Variables	Visit 1	Visit 2	Visit 3	Visit 4	Visit 5	Visit 6	Visit 7	Visit 8	Visit 9		Visit 10+11	
Information visit	X											
Obtain informed consent	X											
Inclusion/exclusion criteria		X										
ECG		X										
Demographics		X										
Length		X										
Medical history		X	X						X			
Date of diagnosis of type 1 diabetes and first insulin injection		X										
Smoking status			X									
Family history of type 1 diabetes		X										
Concomitant medication		X	X	X	X	X	X	X	X			
Physical examination		X	X	X	X	X	X	X	X			
Blood pressure			X		X	X	X	X	X			
Weight		X	X		X	X	X	X	X			
Information regarding type of glucose monitoring			X			X	X	X	X		X	
GAD, ZnT8, insulin/IAA and IA-2-antibodies		X							X			
Mixed Meal Tolerance Test		X	X		X		X		X		X	
HbA1c		X	X		X	X	X	X	X		X	
Proinsulin			X						X			
Hematology†		X	X		X		X		X			
Clinical Chemistry‡		X	X		X		X		X			
Urine pregnancy test		X										
HIV, hepatitis serology, IgA transglutaminase, thyroid status		X										

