### Endpoints

The primary endpoint will be the change in residual insulin secretion measured by stimulated C-peptide 2-hour area under the curve profile measured by MMTT between baseline and week 52. The secondary endpoints are insulin need (U/kg), time in glucose range (3.9–10 mmol/L), time in hypoglycaemia (<3.9 mmol/L) and HbA1c. Exploratory variables include glycaemic variability, well-being, hypoglycaemia confidence, treatment satisfaction and diabetes-related distress. All predefined endpoints are shown in box 1.

Box 1Predefined endpointsPrimary endpointChange in residual insulin secretion measured by stimulated C-peptide 2 hour area under the curve profile measured by mixed meal tolerance test (MMTT) between baseline and week 52.Secondary endpointsChange in mean Insulin dosage per kilo body weight for 24 hours from baseline to week 52.Change in time with glucose levels in range (3.9-10 mmol/l) measured by masked CGM (Libre Pro iQ) from baseline to week 52.Change in time with hypoglycaemia (<3.9 mmol/l) measured by masked CGM (Libre Pro iQ) from baseline to week 52.Difference in HbA1c from baseline to week 52.Exploratory endpointsChange in time in hypoglycaemia (<3.0 mmol/l) measured by masked CGM (Libre Pro iQ) from baseline to week 52.Change in proinsulin/c-peptide ratio in serum as a measure of beta cell stress from baseline to week 52.Change in time in target (3.9-8 mmol/l) measured by masked CGM (Libre Pro iQ) from baseline to week 52.Change in time in hyperglycaemia >10 mmol/l and >13.9 mmol/l measured by masked CGM (Libre Pro iQ) from baseline to week 52.Change in glycaemic variability measured by SD, CV and MAGE by masked CGM (Libre Pro iQ) from baseline to week 52.Change in proportion of patients with peak residual insulin secretion measured by MMTT: stimulated C-peptide >0.4 nmol/mL from baseline to week 52.Change in WHO-5 scores from baseline to week 52.Change in DTSQs scores from baseline to week 52.Change in DTSQc scores estimated at week 52.Change in HCS scores from baseline to week 52.Change in PAID scores from baseline to week 52.Change in IPAQ scores from baseline to week 52.The same variables described above regarding primary, secondary and exploratory endpoints will be evaluated if the variable is measured at a specific time point from baseline to week 4, baseline to week 13 as well as baseline to week 26.

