### Statistical analysis

The full analysis set (FAS-population) consists of all participants who receive at least one dose of study medication and have at least one follow-up measurement.

The per-protocol population (PP-population) consists of all participants in the full analyses set without any significant protocol deviations. The PP-population is defined at the clean file meeting before the database is locked.

The safety population consists of all participants who received at least one dose of study medication.

The primary efficacy variable, difference in change from baseline to week 52 in residual insulin secretion measured by stimulated C-peptide 2 hour area under the curve profile measured by MMTT, will be estimated by ANCOVA adjusting for differences between treatment groups in stimulated C-peptide 2 hour area under the curve at baseline. The secondary efficacy variables (difference in change in insulin need, time in glucose range, time in hypoglycaemia and HbA1c) will also be estimated by ANCOVA adjusting for difference in the evaluated variable at baseline. No interim analyses are planned in the study.

Regarding continuous exploratory variables, the difference between the two groups for normally distributed variables will be analysed using ANCOVA adjusting for baseline value and for not normally distributed variables using Fisher’s non-parametric permutation test. Dichotomous variables will be analysed using Fisher’s exact test and ordered categorical variables using Mantel-Haenszel Chi-square trend test. Statistiska Konsultgruppen, Gothenburg, Sweden, has been consulted for statistical methods.

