### Sample size calculation

In a previous study of 191 individuals with type 1 diabetes followed from diagnosis and year onwards, stimulated c-peptide decreased from 0.70 to 0.46 nmol/L.^6^ The observed SD for c-peptide was 0.34 nmol/L. In two other studies, the SD has been suggested to be 0.25 nmol/L.^22 23^

Using an SD of 0.34 nmol/L, our power calculations indicate that 114 participants would be needed to detect a 25% reduction in c-peptide decline (0.18 nmol/L difference), with two-sided t-test with a power of >80% and significance level of 0.05. If the SD is 0.25 nmol/L, we will also have power to detect a treatment difference of 0.14 nmol/L. We have, therefore, planned to include 114 participants, with an assumed dropout rate of 10%, 127 participants are required.

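### The exploratory C-peptide responder endpoint gets an unadjusted Fisher's exact test, which is valid but gives up power by leaving the measured baseline peak unused and by being conservative

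*Protocol article*

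**What the plan says.** The Statistical analysis section of the protocol article sets one rule for all binary variables: "Dichotomous variables will be analysed using Fisher’s exact test and ordered categorical variables using Mantel-Haenszel Chi-square trend test". It names no covariate or stratification.

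Box 1 (Endpoints) contains one dichotomous efficacy endpoint, listed as exploratory: "Change in proportion of patients with peak residual insulin secretion measured by MMTT: stimulated C-peptide >0.4 nmol/mL from baseline to week 52". The closing lines of Box 1 extend each endpoint to earlier time points where the variable is measured. For this endpoint the relevant schedule is in Study visits: "MMTT will be performed at randomisation, week 4, 26 and 52". A baseline peak is therefore planned for every participant, and the endpoint can be evaluated at weeks 4, 26 and 52.

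Other variables are treated differently. The primary and secondary variables get ANCOVA on their baseline value. For continuous exploratory variables, "the difference between the two groups for normally distributed variables will be analysed using ANCOVA adjusting for baseline value". Exploratory variables that are not normally distributed get a permutation test, and ordered categorical ones a Mantel-Haenszel trend test, neither with a stated baseline adjustment.

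**The concern.** The endpoint is described as a change from baseline, yet the stated test has no place for a continuous baseline value. Baseline peak C-peptide is a natural predictor of being above the cut-off a year later, it comes from the same test as the primary endpoint, and it costs nothing extra to use. Fisher's exact test is also conservative at this sample size, so power is lost for two separate reasons.

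What is at stake is modest. At the effect the trial is designed to detect, the responder comparison succeeds about half the time, while the primary comparison is sized for at least 80%. A non-significant responder result could then be read as contradicting a real C-peptide effect.

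**Working it through.** **Inputs.** From Sample size calculation: "stimulated c-peptide decreased from 0.70 to 0.46 nmol/L" gives the baseline and one-year control means; SD 0.34 (alternative 0.25); target difference 0.18 (0.14 with the smaller SD); 114 evaluable participants; two-sided 5% level.

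Assumptions not in the document:
- 1:1 allocation.
- Cut-off read as 0.4 nmol/L. It is printed in nmol/mL, while the other C-peptide values are in nmol/L.
- The quoted stimulated C-peptide figures stand in for the peak.
- Distribution shape, and the correlation rho between baseline and week 52.

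**Step 1: reproduce the plan's figure.** n per arm = 2 × (1.96 + 0.842)² × 0.34² / 0.18² = 56.01, rounded up to 57, so 114 in total. Noncentral-t power at 57 per arm is 80.0%. 114 / 0.90 = 126.7, so 127. Both stated numbers reproduce. The document gives no power for the responder endpoint.

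**Step 2: responder rates implied by the design effect (normal model).**
- Placebo: Φ((0.46 − 0.40)/0.34) = Φ(0.176) = 57%.
- Active, mean 0.46 + 0.18 = 0.64: Φ((0.64 − 0.40)/0.34) = Φ(0.706) = 76%.

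**Step 3: hand check of an unadjusted, non-exact test.** Pooled proportion 0.665. Null SE = √(2 × 0.665 × 0.335 / 57) = 0.0884. Alternative SE = √((0.57 × 0.43 + 0.76 × 0.24)/57) = 0.0866. Power ≈ Φ((0.19 − 1.96 × 0.0884)/0.0866) = Φ(0.19), about 58%. This agrees with the simulated 58–63% below.

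**Step 4: simulated power, 57 per arm, SD 0.34, difference 0.18.** LR is the likelihood-ratio test in a logistic model; adjusted means with continuous baseline peak. Run A: 1,500 trials per rho, no entry floor. Run B: 4,000 trials per rho, baseline truncated at the 0.20 entry floor. Run C: a separate simulation on the same inputs.

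| Run | rho | Fisher | Unadjusted LR | Adjusted LR | Total gap | Conservatism | Baseline omitted |
|---|---|---|---|---|---|---|---|
| A | 0.3 | 49.8 | 58.5 | 60.8 | 11.0 | 8.7 | 2.3 |
| A | 0.5 | 52.1 | 59.1 | 66.7 | 14.6 | 7.0 | 7.6 |
| A | 0.7 | 50.1 | 60.1 | 74.7 | 24.6 | 10.0 | 14.6 |
| B | 0.3 | 50.4 | 59.4 | 60.0 | 9.6 | 9.0 | 0.6 |
| B | 0.5 | 53.0 | 60.6 | 66.4 | 13.4 | 7.6 | 5.8 |
| B | 0.7 | 55.3 | 62.7 | 75.0 | 19.7 | 7.4 | 12.3 |
| C | 0.3 | 51 | 60 | 62 | 11 | 9 | 2 |
| C | 0.5 | 51 | 58 | 66 | 15 | 7 | 8 |
| C | 0.7 | 52 | 60 | 75 | 23 | 8 | 15 |

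Conservatism is unadjusted LR minus Fisher; baseline omitted is adjusted LR minus unadjusted LR. Taking the runs together, conservatism costs about 7–9 points (one run reaches 10) and omitting baseline about 2–15 (one run gives under 1 at rho 0.3).

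**Step 5: type I error under no effect.** Fisher's test rejects in 2.6–3.3% of run-A null trials and 2.1–3.4% across the other null scenarios. The adjusted test rejects in 5.1–6.0% and 4.5–6.1%.

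**Step 6: other assumptions, rho 0.3 to 0.8.**

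| Model | Total gap (points) | Part from omitting baseline |
|---|---|---|
| Normal, SD 0.34, difference 0.18, entry floor | 10–27 | 1–19 |
| Normal, SD 0.25, difference 0.14, entry floor | 11–30 | 2–22 |
| Lognormal, difference 0.12 | 12–31 | 4–23 |
| Lognormal, difference 0.18 (Fisher power about 88%) | 6–11 | 2–7 |

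**The case against.** The strongest reply is that nothing here is an error. Fisher's exact test on a randomised comparison controls type I error. The endpoint is exploratory, one of many in Box 1, with no power target, and simple unadjusted tests are also given to non-normal and ordered exploratory variables. All of that stands, and it limits the point to efficiency.

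The power figures also rest on assumptions. Rho is not given. The normal model puts Φ(−0.46/0.34), about 9%, of placebo week-52 values below zero. Without truncation it puts Φ(−0.50/0.34), about 7%, of baseline values below the entry floor. Under a lognormal shape with the full 0.18 difference, the gap shrinks to 6–11 points. This stands too, which is why a range is given.

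A reader might infer that Fisher's test cannot reflect baseline at all and so contradicts the endpoint. The document does not support that, because it does not say how the change in proportion is to be tabulated. A table of retained against lost status would bring in dichotomised baseline status. That would probably recover only part of the information: in run B, adjusting a logistic model for baseline status above or below 0.4 changed power over the unadjusted test by about 0, 2 and 6 points at rho 0.3, 0.5 and 0.7, against 1, 6 and 12 for the continuous value.

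Part of the adjusted test's gain comes from working at about 5–6% rather than 3%. The split in the table isolates most of this as conservatism.

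**Conclusion.** The point holds as a loss of efficiency on an exploratory endpoint. On the plan's own means, SD and target difference, Fisher's exact test has about 50–55% power against about 61–75% for baseline-adjusted logistic regression at rho 0.3–0.7. The total gap runs from about 6 to 31 points over the wider set of assumptions. It depends on rho, the distribution, 1:1 allocation, the cut-off being 0.4 nmol/L and the quoted C-peptide figures serving for the peak.

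Two stronger readings are tempting and should not be drawn. One is that the whole gap comes from ignoring baseline: about 7–9 points would be recovered by any non-exact unadjusted test, and at rho 0.3 these are most of the gap. The other is that the responder result would be biased, or would threaten the primary conclusion. Randomisation keeps the unadjusted comparison valid, its type I error already allows for chance baseline imbalance, and the primary endpoint is analysed separately by ANCOVA with baseline. Adjustment would make a discordant responder result less likely but would not remove the possibility.

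**What to change.** In the Statistical analysis section, take the C-peptide responder endpoint out of the general rule for dichotomous variables. At weeks 4, 26 and 52, analyse it by logistic regression on treatment and continuous baseline peak C-peptide, tested by likelihood ratio. Report the marginal (standardised) difference in proportions with its 95% confidence interval. Keep Fisher's exact test as a sensitivity analysis, and as the method for rare events or if the model does not converge.

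The cost is a short change of wording before unblinding, with no new data or visits. The small downside is a model-based test whose type I error is approximate rather than exact, about 5–6% in simulation.

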### Sample size calculation

In a previous study of 191 individuals with type 1 diabetes followed from diagnosis and year onwards, stimulated c-peptide decreased from 0.70 to 0.46 nmol/L.^6^ The observed SD for c-peptide was 0.34 nmol/L. In two other studies, the SD has been suggested to be 0.25 nmol/L.^22 23^

Using an SD of 0.34 nmol/L, our power calculations indicate that 114 participants would be needed to detect a 25% reduction in c-peptide decline (0.18 nmol/L difference), with two-sided t-test with a power of >80% and significance level of 0.05. If the SD is 0.25 nmol/L, we will also have power to detect a treatment difference of 0.14 nmol/L. We have, therefore, planned to include 114 participants, with an assumed dropout rate of 10%, 127 participants are required.

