### Randomisation

If inclusion criteria are fulfilled, randomisation will take place no later than 8 weeks later. The participants will be randomised to either treatment with an IL-17 inhibitor (ixekizumab) or placebo.

A randomisation list will be created for each participating site. The lists are created by Statistiska Konsultgruppen, Gothenburg, and sent to Tamro AB, Gothenburg, which is responsible for delivering the study medications to each participating site. Only designated personnel from Statistiska Konsultgruppen and Tamro AB will have access to the randomisation lists. If a participant discontinues study participation, their randomisation number will not be reused, and the subject will not be allowed to re-enter the study again.

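### The sample-size section calls 0.18 nmol/L a 25% reduction in C-peptide decline, but on its own cited figures it is a 75% reduction, so the stated power does not apply to the effect named in words

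*Protocol article*

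**What the plan says.** All the relevant figures stand in the Protocol article, section Sample size calculation.

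- Reference cohort: "stimulated c-peptide decreased from 0.70 to 0.46 nmol/L".
- Variability: "The observed SD for c-peptide was 0.34 nmol/L", with a smaller alternative: "In two other studies, the SD has been suggested to be 0.25 nmol/L".
- Target: "114 participants would be needed to detect a 25% reduction in c-peptide decline (0.18 nmol/L difference". The basis is a t-test at a two-sided level of 0.05, and the power claimed is above 80%.
- Second scenario, in absolute units only: "If the SD is 0.25 nmol/L, we will also have power to detect a treatment difference of 0.14 nmol/L".
- Enrolment: "planned to include 114 participants, with an assumed dropout rate of 10%, 127 participants are required".

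The Randomisation section names two arms but gives no allocation ratio. No other section gives a different expected decline or another basis for the 25%.

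**The concern.** The section reports a decline and then defines its target as a percentage reduction of C-peptide decline, with an absolute difference in brackets as its equivalent. The two do not match on the figures just given. One of them must be wrong, and the wording errs in the favourable direction: it attaches more than 80% power to an effect a third the size of the one used in the calculation.

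This sentence tells readers what effect on the primary endpoint the trial was built to detect. Someone who relies on the percentage would believe the trial is well placed to find a modest slowing of C-peptide loss. Someone who relies on the absolute figure would see that it is powered for a large one.

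**Working it through.** **Inputs.** From Sample size calculation: baseline 0.70, later value 0.46, SD 0.34 (alternative 0.25), target 0.18 (alternative 0.14), two-sided alpha 0.05, 114 evaluable, 10% dropout. Assumed: 1:1 allocation, so 57 per arm.

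**Step 1: reproduce the plan's N.**
- Normal approximation: n per arm = 2 × (1.960 + 0.842)² × SD² / d² = 2 × 7.85 × 0.34² / 0.18² ≈ 56.0, just above 56, so 57 per arm and 114 in total.
- The exact noncentral-t calculation also gives 57 per arm, with power 80.0% (80.7% by the normal approximation).
- Dropout: 114 / 0.90 = 126.7, so 127.
- A one-sided test would need only 45 per arm and does not match.

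The calculation therefore used 0.18 nmol/L. The 1:1 assumption is supported because it returns the stated N.

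**Step 2: express the differences relative to the cited decline.**
- Decline: 0.70 − 0.46 = 0.24 nmol/L.
- 25% of the decline: 0.25 × 0.24 = 0.06 nmol/L.
- Main target: 0.18 / 0.24 = 75% of the decline. Allowing for rounding of the published values, the range is 0.175 / 0.25 = 70% to 0.185 / 0.23 = 80%.
- Main target against the baseline level: 0.18 / 0.70 = 25.7%; conversely, 0.25 × 0.70 = 0.175.
- Second scenario: 0.14 / 0.24 = 58% of the decline.

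**Step 3: power at 57 per arm (two-sided t-test).** The standard error is SD × √(2/57), which is 0.0637 at SD 0.34 and 0.0468 at SD 0.25.

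| True difference (nmol/L) | Share of 0.24 decline | Power, SD 0.34 | Power, SD 0.25 |
|---|---|---|---|
| 0.18 | 75% | 80.0% | 96.8% |
| 0.14 | 58% | 58.7% | 84.2% |
| 0.12 | 50% | 46.3% | 71.9% |
| 0.06 | 25% | 15.4% | 24.6% |

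For 80% power at 0.06 nmol/L, the same test would need 506 per arm (1,012 evaluable) at SD 0.34, or 274 per arm (548) at SD 0.25.

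**Step 4: sensitivity of the 15% figure.**
- No dropout, 63 per arm, SD 0.34: 16.6%.
- Baseline-adjusted ANCOVA, as planned in Statistical analysis, taking 0.34 as the SD of the C-peptide level and the residual SD as 0.34 × √(1 − r²). The document gives no correlation r, so a range is assumed:

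| r | Residual SD | Power for 0.06 |
|---|---|---|
| 0.5 | 0.294 | 19.0% |
| 0.6 | 0.272 | 21.5% |
| 0.7 | 0.243 | 25.8% |
| 0.8 | 0.204 | 34.4% |

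**Step 5: smallest significant observed difference.** With the t critical value of 1.98 on 112 degrees of freedom, this is 1.98 × 0.0637 = 0.126 nmol/L at SD 0.34 (53% of the decline) and 1.98 × 0.0468 = 0.093 at SD 0.25 (39%).

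**The case against.** The strongest reply is that this is a mislabel and not a power error. The section never mentions 0.06 nmol/L. It prints the operative difference in the same phrase, and N, test, alpha and dropout all follow correctly from it. The second scenario is given only in absolute units and holds as stated. All of this stands, and it means that the design does not have to change. It does not remove the contradiction: the sentence gives the percentage as the effect and the 0.18 as its equivalent, and they are not equivalent.

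Three further qualifications also stand.

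- The 15% uses the section's unadjusted t-test, whereas the primary analysis is ANCOVA. The figure should be tied to that basis. Power for 0.06 stays low under each correlation examined at SD 0.34.
- The 75% and 58% assume that the cited cohort's 0.24 nmol/L is the relevant decline. The article's description of that cohort's follow-up is loose, and it states no separate assumption for this trial's placebo arm. The percentages should be presented as relative to that cohort.
- That the authors meant 25% of the baseline level is plausible, since 0.175 is close to 0.18, but it is an inference.

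A reader might go further and infer that the drug must stop three quarters of the loss for the trial to succeed. That confuses the effect powered at 80% with the effect needed for significance. At SD 0.34 an observed difference of about 0.126 nmol/L would already be significant, and a true 50% reduction has 46% power.

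A reader might also infer that a non-significant result could never exclude a 25% to 50% slowing. That depends on the estimate. At SD 0.34, an observed difference below about −0.006 (0.12 − 0.126) would exclude a 50% slowing, and one below about −0.066 (0.06 − 0.126) would exclude a 25% slowing.

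**Conclusion.** The point holds as an internal contradiction in the stated target effect. On the section's own figures, 0.18 nmol/L is a 75% reduction of the cited decline (70–80% allowing for rounding), not 25%. The power statement belongs to 0.18 nmol/L and does not apply to the effect named in words, for which power is about 15% at SD 0.34 and about 25% at SD 0.25.

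These figures rest on 57 evaluable participants per arm under assumed 1:1 allocation, a two-sided t-test at 0.05, and the cited cohort's decline of 0.24 nmol/L. Under ANCOVA at SD 0.34 with an assumed baseline correlation of 0.5–0.8, the first becomes about 19–34%.

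The documents do not support saying that the sample size was miscalculated: 114 and 127 are correct for 0.18 nmol/L. The label still has to be corrected, because it misstates the primary endpoint's detectable effect threefold in the favourable direction.

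**What to change.** Keep N. In the sample-size section, and wherever the target is repeated:

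1. State the target as 0.18 nmol/L, about 75% of the 0.24 nmol/L decline in the cited cohort, or about 25% of that cohort's baseline level.
2. State the second scenario, 0.14 nmol/L at SD 0.25, as about 58% of the same decline.
3. State that on the same t-test basis (SD 0.34, 57 per arm) power for a 25% reduction in decline, 0.06 nmol/L, is about 15%.
4. Say that a non-significant primary result will be interpreted from the confidence interval for the treatment difference, without declaring in advance which effects it will or will not exclude.

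The cost is a wording correction, best made before unblinding so that it cannot look like a reinterpretation of the result. The stated detectable effect becomes less favourable. There are no extra participants and no change to endpoint, analysis or conduct.
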